### Statistical Analysis

Data will be analyzed using the SPSS statistical software package (version 20.0, SPSS, Inc., Chicago, IL). Normality of the distribution for all outcome measures will be assessed using the Kolmogorov Smirnov test. Analyses will include standard descriptive statistics, t tests, correlation, regression and two-way repeated measures ANOVA or the comparable non-parametric test as necessary to examine differences between and within groups, at baseline and weeks 8, 12, and 20.

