### Primary outcomes

#### Fatigue

Fatigue will be measured using The Functional Assessment of Cancer Therapy: Fatigue (FACT-F) questionnaire, which reports weekly fatigue on a scale of 0–52, with higher values indicating less fatigue [45]. The FACT-F has shown good reliability and validity (Cronbach’s α: 0.93-0.94) for predicting clinically significant treatment outcomes of CRF [46].

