### Sample Size Calculation

Sample size calculations were complete using Vanderbilt Power and Sample Size software (Vanderbilt University, TN). Combined diet and exercise interventions with CRF as an outcome are relatively limited. A diet and exercise intervention in men treated with ADT showed prostate cancer-specific CRF (as measured by FACT-F) scores improved by 3.7 – 14.2 (CI, 95%; adjusted mean 8.9 points) in the intervention group compared to the control group [20]. Assuming FACT-F scores for this group were normally distributed with a SD of 8.9, a true difference between the experimental and control arms of 5.2, and a power of 0.8, we would need 47 experimental and control participants to be able to reject the null hypothesis. The type 1 error probability associated with this test of the null hypothesis is 0.05. With an anticipated 20% attrition rate based on previous research from our laboratory, we would need 58 experimental and control group participants to be able to reject the null hypothesis.

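### A normality test on the outcome data can switch the FACT-F analysis from repeated measures ANOVA to an unnamed rank test, so the hypothesis and estimand are not fixed in advance

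*Protocol article*

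**What the plan says.** The Statistical Analysis section of the protocol article makes two linked statements. First, "Normality of the distribution for all outcome measures will be assessed using the Kolmogorov Smirnov test". Second, the analyses are to include descriptive statistics, t tests, correlation, regression and "two-way repeated measures ANOVA or the comparable non-parametric test as necessary", applied to differences between and within groups at baseline and weeks 8, 12 and 20. The section does not say outright that the first result triggers the second choice, but it gives no other use for the normality test.

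Three other places matter:

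- The Fatigue section says the FACT-F "reports weekly fatigue on a scale of 0–52, with higher values indicating less fatigue", so the score is bounded.
- The Sample Size Calculation treats the same score as normal ("Assuming FACT-F scores for this group were normally distributed with a SD of 8.9") and sizes the trial on "a true difference between the experimental and control arms of 5.2, and a power of 0.8".
- The two aims at the end of the Background are both comparisons between arms: nutrition therapy against usual care at 12 weeks, and nutrition therapy plus interval training against usual care at 20 weeks.

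**The concern.** The sample size rests on a difference in mean FACT-F. The analysis section then makes it depend on the data whether a mean-based analysis is used at all. Three things follow.

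- **The check looks at the wrong quantity.** ANOVA and t tests need roughly normal residuals, or enough participants for the mean difference to behave well. They do not need normal raw scores.
- **The usual substitutes answer different questions.** Friedman and Wilcoxon signed-rank tests look at change within an arm. Mann-Whitney compares arms at one visit and, on raw scores, ignores baseline. None of them tests group-by-time, and none gives an estimate on the 5.2-point scale.
- **The switch can fall differently for different outcomes.** The rule covers every outcome measure, so one questionnaire could be reported as a mean difference and another as a rank comparison, depending on how each sample happened to look.

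What is at stake is whether the trial's main result will be an estimate of the quantity it was powered for.

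**Working it through.** **1. The plan's own sample size.** Inputs from the Sample Size Calculation: difference 5.2, SD 8.9, power 0.80, alpha 0.05 (taken as two-sided, which reproduces the stated figure).

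n per arm = 2 × (1.960 + 0.842)² × 8.9² / 5.2² = 2 × 7.85 × 79.21 / 27.04 ≈ 46.

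Solving with the t distribution gives 46.96, so 47 per arm, as stated. Dividing by 0.80 for attrition gives 58.75 against the stated 58, a rounding matter with no bearing here. The trial is therefore sized on a two-sample comparison of means.

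**2. How often would the normality test reject for FACT-F?** The documents give the range (0–52) and the SD (8.9), but no mean, skewness or proportion at the ceiling. These have to be assumed. Two shapes were simulated as integer scores on 0–52:

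- a normal with the stated mean and SD 8.9, clipped at 0 and 52;
- a beta on 0–52 with μ = mean/52, k = μ(1 − μ)/(8.9/52)² − 1, a = μk and b = (1 − μ)k. At mean 38: μ = 0.731, k = 5.72, a = 4.18, b = 1.54.

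The table gives the rejection rate at the 5% level for one sample of 47 (one arm, one visit), with the mean and SD estimated from the sample.

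| Assumed mean | Clipped normal, Lilliefors | Beta, Lilliefors | Beta, plain KS |
|---|---|---|---|
| 30 | 6–9% | 11–12% | 0% |
| 34 | 8–9% | 21% | 0% |
| 38 | 9% | 45% | 2% |
| 40 | 14% | 66% | 5% |
| 42 | 27% | 89% | 17% |
| 44 | 58–59% | 100% | 57% |

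Repeat runs differ by up to about three percentage points. Boundedness alone does not cause rejection: at means of 30 to 38 the clipped normal is rejected only slightly more often than the nominal 5%. Pooling all 116 participants raises the Lilliefors rates to 16–99% (clipped normal) and 29–100% (beta) over the same means.

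**3. Does the unit of testing matter?** There are 2 arms × 4 visits = 8 cells. With the beta shape, 47 per arm and an assumed within-person correlation of 0.6:

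| Assumed mean | One cell rejects | Either arm rejects at week 20 | Any of 8 cells rejects |
|---|---|---|---|
| 30 | 10% | 20% | 58% |
| 34 | 20% | 37% | 81% |
| 38 | 43% | 69% | 98% |

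A rough check that ignores the correlation, at mean 30: 1 − 0.90² = 0.19 and 1 − 0.90⁸ = 0.57. The same data would lead to different analyses depending on which cells are tested.

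**4. What happens to type I error?** The rule simulated at week 20, with 47 per arm and 5,000 runs, was: apply the normality test, then use a t test or Mann-Whitney. Followed mechanically, it gives a type I error of 0.047–0.055. Taking the smaller of the two p-values gives 0.051–0.072. The nominal level is 0.05.

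**The case against.** The strongest reply is that little harm follows. Both aims compare randomized arms, and a Mann-Whitney test at week 12 or 20 is a valid comparison of those arms; on change scores it compares change directly. A single-visit t test, which the section also lists, omits baseline too. Rank-based factorial methods that test group-by-time exist (the ANOVA-type statistic and the aligned rank transform), and the plan may intend one. It names neither Friedman nor Mann-Whitney. Following the rule mechanically leaves type I error near nominal. Distribution also plainly matters for some outcomes, such as IL-6, IL-8 and PSA. Finally, this is a condensed article, and a separate analysis plan may name the fallback, the test level and the unit tested.

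Much of this stands, and it rules out several stronger readings that a reader might infer:

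- That FACT-F will usually end up on the fallback. The rate depends on inputs the documents do not give.
- That no non-parametric test of group-by-time exists. Such methods do exist.
- That the fallback could not answer either aim. It could still compare the arms.
- That the unnamed details are in themselves a defect. They may properly sit in an analysis plan.

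What the reply does not remove is the rule itself. The data-dependent choice is in the published text, and naming the fallback elsewhere would still leave the primary estimand dependent on a preliminary test.

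**Conclusion.** The point holds in a limited form. The Statistical Analysis section lets a normality result on the outcome values decide between a mean-based analysis and an unnamed non-parametric one. For FACT-F the switch may happen. Its probability is not determined by the documents: per arm and visit it is about 6–58% (clipped normal) or 12–100% (beta) with the Lilliefors correction, and about 0–5% with the plain test for means up to 40. These figures assume means of 30 to 44, SD 8.9 and 47 per arm; the means and shapes are assumptions.

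The harm is that the hypothesis and estimand are not fixed before the data are seen and may differ between outcomes, so the reported result may not be the 5.2-point mean difference used for sizing. A reader might infer a serious inflation of false positives, but the simulated error rates do not support that. The sample size itself is unaffected. The matter deserves correction because a better rule is readily available, not because the trial would otherwise be invalid.

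**What to change.** - Remove the Kolmogorov-Smirnov test as a gate for choosing the analysis.
- Fix in advance one baseline-adjusted, mean-based comparison of FACT-F between arms at weeks 12 and 20: ANCOVA, or a mixed model with baseline FACT-F as a covariate. Baseline FACT-F is already collected under Table 1.
- Check residuals graphically.
- Report a bootstrap or robust-standard-error interval for the same mean difference, or a named rank method, only as a sensitivity analysis.
- State in advance which biomarkers will be log-transformed.

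The cost is a change of wording and a little extra analysis work. Sample size, visits and data collection do not change.

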Dietary manipulation has been identified to be an important lifestyle factor to alleviate ADT related side effects [32–34]; yet the efficacy of dietary interventions in isolation during treatment or into prostate cancer survivorship are limited for supporting the adverse side effects seen from ADT. Importantly, prostate cancer-specific dietary guidelines provide limited support and guidance for alleviating adverse treatment-related side effects, including CRF [35, 36]. In non-oncological populations, structured individualized nutrition therapy by an Accredited Practising Dietitian is recommended for adults who are overweight, obese, insulin resistant, and have altered lipid and triglyceride metabolism [37–39]; all notable adverse side effects from ADT. Yet the translation of this nutrition therapy in prostate cancer is yet to be elucidated. Recently, a Mediterranean-style diet pattern has been shown to improve metabolic and cardiovascular parameters in men at risk of prostate cancer [40]. Adherence to an anti-inflammatory properties of a Mediterranean diet have shown small reductions in hypertension (reduced systolic blood pressure; SE = – 1.44mm Hg [95% CI, -2.88 – 0.01]; and diastolic blood pressure; SE = -0.70mm Hg [95% CI, -1.34 – 0.07) [41], and risk of type 2 diabetes (RR = 0.93; 95% CI, 0.89 – 0.98) [42]; thus showing plausible metabolic and cardiovascular effects on known ADT related side effects. Yet practical application of the Mediterranean-style diet pattern to men treated with ADT for management of CRF and improving quality of life is yet to be ellucidated.

Literature to date has encompassed general healthy eating guidelines for the management of prostate cancer treated related side effects [19, 20, 31], however general guidelines do not take into account the specific dietary requirements needed to manage the ADT-related side effects. Therefore, the role of specific individualized nutrition therapy tailored to alleviate the side effects of ADT, particularly CRF, and improve quality of life warrants investigation.

This study aims to:Investigate whether 12-weeks of nutrition therapy, compared to 12 weeks of usual care, can improve prostate CRF and quality of life in men treated with ADT.Assess the combined benefits of 20-weeks of nutrition therapy with 8-weeks of high intensity exercise (weeks 12–20), compared to 20 weeks of usual care, on CRF and quality of life in men treated with ADT.

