We hypothesized that 12-weeks of nutrition therapy, compared to 12 weeks of usual care, will improve CRF and quality of life in men with prostate cancer treated with ADT. It is further hypothesized a 20-week nutrition therapy intervention with 8 weeks of high intensity interval training, compared to 20 weeks of usual care, will improve CRF and quality of life in men with prostate cancer treated with ADT. Secondary measures of body composition, functional capacity, metabolic syndrome and biomarkers such as prostate specific antigen, insulin like growth factor [43]-1, IGF-2, IGF binding protein-3, interleukin [IL]-6, and IL-8), will be measured and analyzed between and within groups. We hypothesis nutrition therapy alone, and with high intensity exercise will improve body composition, functional capacity, and biomarkers of metabolic syndrome and prostate cancer progression.

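### The only longitudinal method named, a four-visit repeated-measures ANOVA, does not by itself test the week-12 and week-20 hypotheses and suits a trial expecting 20% attrition poorly (should-fix)

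*Protocol article*

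**What the plan says.** Protocol article, Statistical Analysis: "Analyses will include standard descriptive statistics, t tests, correlation, regression and two-way repeated measures ANOVA or the comparable non-parametric test as necessary". The only longitudinal entry in that list is "two-way repeated measures ANOVA or the comparable non-parametric test as necessary to examine differences between and within groups". The methods are to be used "to examine differences between and within groups, at baseline and weeks 8, 12, and 20". The software is SPSS version 20; the procedure within it is not named. No method is called primary, and none is linked to a hypothesis.

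Protocol article, Background: the first hypothesis reads "We hypothesized that 12-weeks of nutrition therapy, compared to 12 weeks of usual care, will improve CRF and quality of life". The second concerns a "20-week nutrition therapy intervention with 8 weeks of high intensity interval training, compared to 20 weeks of usual care, will improve CRF". Both are between-arm comparisons at a named time.

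Protocol article, Sample Size Calculation: a single comparison of two means, SD 8.9, difference 5.2, power 0.8, type 1 error 0.05, giving 47 per arm. "With an anticipated 20% attrition rate based on previous research from our laboratory", this becomes 58 per arm, 116 in all.

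**The concern.** The intervention changes at week 12, when interval training is added to the diet. Which visit shows a difference is therefore the scientific question. A two-way ANOVA over four visits gives two tests of arm, and neither answers it directly. The group main effect averages in the baseline visit, where randomisation guarantees no true effect. The group-by-time test has 3 degrees of freedom and does not locate the difference.

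Three further points follow from the design:
- The trial was sized on neither test.
- Baseline FACT-F enters the ANOVA as one more outcome level. The interaction does compare change from baseline, but the precision that a covariate would give is not taken.
- The classical form of the method needs a complete set of visits. Supervised training three times a week starts at week 12 in one arm only, so selective loss from that arm is plausible.

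At stake are power for the stated hypotheses, a possible completers bias, and freedom to choose among several tests after the data are in.

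**Working it through.** **1. The plan's own figure.** Inputs from Sample Size Calculation: difference 5.2, SD 8.9, power 0.8, alpha 0.05. A two-sided two-sample t test with 47 per arm has power 0.8003; with 46 it has 0.7916. So 47 is reproduced, and the trial rests on one two-group contrast. Attrition: 47/0.8 = 58.75, which the article gives as 58. Conversely 58 × 0.8 = 46.4 completers per arm.

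**2. Power of the group-by-time test.** Assumptions, not in the article: true arm differences d = (0, 1.7, 2.6, 5.2) at baseline and weeks 8, 12, 20; equal correlation r between visits; 47 complete men per arm.

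- Mean of d: 9.5/4 = 2.375. Deviations: −2.375, −0.675, 0.225, 2.825. Sum of squares: 5.641 + 0.456 + 0.051 + 7.981 = 14.13.
- Noncentrality: λ = (47/2) × 14.13 / [8.9² × (1 − r)] = 4.19/(1 − r), referred to F with 3 and 3 × 92 = 276 degrees of freedom.

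**3. Power of the baseline-adjusted week-20 contrast.** Residual SD = 8.9 × √(1 − r²); standard error = residual SD × √(2/47); power ≈ Φ(5.2/SE − 1.96). For r = 0.5: 8.9 × 0.866 = 7.71; SE = 1.59; 5.2/1.59 = 3.27; power 0.90.

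| r | λ | group-by-time, formula | group-by-time, simulated | adjusted week 20, simulated |
|---|---|---|---|---|
| 0.3 | 5.99 | 51% | 53% | 84% |
| 0.5 | 8.38 | 67% | 66% | 90% |
| 0.6 | 10.48 | 78% | 78% | 93% |
| 0.7 | 13.97 | 89% | 89% | 98% |

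The unadjusted week-20 contrast stays at 80–81% throughout. The formula for the adjusted contrast gives 84%, 90%, 94% and 98%.

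**4. Other shapes of effect** (simulated, 46 per arm, r = 0.3 / 0.5 / 0.7). Gradual (2.6, 3.9, 5.2): interaction 53 / 68 / 90%, adjusted week 20 about 83 / 89 / 97%. Whole effect at week 20 only: interaction 67 / 82 / 97%, adjusted week 20 about 83 / 88 / 97%. With an abrupt effect and r near 0.7 the gap is almost gone.

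**5. Complete-case numbers.** Dropout alone leaves 46.4 per arm, which the inflation to 58 covers. If a further 5% missed each of weeks 8 and 12 (assumed), 58 × 0.8 × 0.95² = 41.9 remain and t-test power is 74–75%. At an assumed 10%, 58 × 0.8 × 0.90² = 37.6 remain, with power about 70%.

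**6. Selective dropout.** Assume 18% of the intervention arm leave because of fatigue at week 12, and 20% of controls leave at random. Let s be the upward shift this causes in the intervention completers' mean week-12 score. Under equal correlations, their baseline and week-20 means each shift by r·s.

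- Raw week-20 difference: bias r·s.
- Change to week 20: r·s − r·s = 0.
- Change to week 12: s − r·s = (1 − r)·s.

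For example, a raw week-20 difference of 6.2 against a true 5.2, at r = 0.6, implies s = 1.0/0.6 = 1.67. The week-12 change bias is then 0.4 × 1.67 = 0.67, so 3.3 against a true 2.6. Simulations over several dropout mechanisms gave raw week-20 differences of 5.9 to 6.9. The week-20 change stayed at 5.2 under equal correlations and was about 5.4 under decaying ones. The week-12 change was 3.1 to 4.0 against 2.6.

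**The case against.** The strongest reply is that the section offers a menu. T tests could supply the week-12 and week-20 contrasts, and regression could supply baseline adjustment. SPSS also has a mixed-model procedure. An article may leave the analysis population, missing-data rules and model detail to a fuller document. Attrition is already budgeted, and the unadjusted week-20 contrast keeps its planned 80%, so the extra precision is a gain forgone and not an error. All of this stands, and it limits the point to a better choice of method.

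Four stronger readings are tempting, and the article does not support them:
- **That repeated-measures ANOVA is the sole or primary engine, with no baseline adjustment anywhere.** No primary method is named, and regression stands in the same sentence.
- **That men with a missed visit will be dropped.** That is a property of the classical procedure; the article does not state it.
- **That completers bias would inflate the ANOVA's week-20 result by about a point.** That figure belongs to a raw week-20 difference. The group-by-time test compares change, and the week-20 change is nearly unbiased under equal correlations.
- **That within-group change is to count as evidence of efficacy.** The article lists within-group comparisons, but both aims and both hypotheses are against usual care.

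What the reply does not remove: a list with no link to the hypotheses leaves the choice of test open, and the one longitudinal method on it fits neither the hypotheses nor the sizing.

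**Conclusion.** The point holds as a should-fix. The named longitudinal method is valid in itself but poorly matched to two time-specific between-arm hypotheses, to a sample size built on one two-sample comparison, and to 20% expected attrition.

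Under a gradual effect, the interaction test falls short of the planned 80% at correlations up to about 0.6, while the baseline-adjusted week-20 contrast exceeds it throughout. These figures rest on an assumed trajectory and equal visit correlations. With high correlation, or an abrupt effect, the loss is small.

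Bias from selective dropout is possible, but its size and the visit affected depend on the correlation structure. The week-12 change contrast, which bears on the first hypothesis, is the more exposed.

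**What to change.** Name one primary analysis, before any comparison of the arms is seen:

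- **Model:** a linear mixed model for repeated measures (SPSS MIXED).
- **Population:** all randomised men with any post-baseline score, in the arm assigned.
- **Terms:** FACT-F at weeks 8, 12 and 20 as outcomes; baseline FACT-F as covariate; visit, arm and arm-by-visit; unstructured covariance.
- **Report:** adjusted arm differences with 95% confidence intervals at weeks 12 and 20. Conclusions rest on these contrasts, and within-group changes are descriptive.

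The model uses the earlier scores of men who leave, so it is protected where dropout depends on recorded fatigue, though not where it depends on unrecorded scores. It does not add power for a week-12 effect smaller than the 5.2 points used for sizing.

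The cost is wording in the protocol or analysis plan. Data, visits, software and sample size are unchanged. If a separate analysis plan already specifies such a model, the article's list should point to it.

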### Data Collection, Management and Monitoring

The principle investigator and trained research assistants will collect anthropometric, diet, exercise and lifestyle data from the study participants. Inter- and intra-tester reliability will be determined for data collecting investigators and research assistants for all outcome measures as appropriate. Computer files containing study data will be de-identified and password protected with access only available to study investigators. All research notes and data will be kept in a securely locked filing cabinet at The University of Queensland School of Human Movement and Nutrition Sciences. The investigators will comply with the Good Clinical Practice (GCP) guidelines adopted by the Therapeutic Goods Administration and document all adverse events through the Human Research Ethics Committee (HREC). The study investigators will permit study-related monitoring, audits, and inspections by Mater HREC of all study related documents (e.g. source documents, regulatory documents, data collection instruments, study data) and study facilities (e.g. diagnostic laboratory). This study will be conducted in full conformance with the principles of the ‘Declaration of Helsinki’ according to international standards of GCP guidelines, applicable Australian government regulations and Institutional research policies and procedures.

## Discussion

CRF is a distressing and prolonged symptom associated with prostate cancer treatment. Management of CRF is critical for improving quality of life during and after treatment for prostate cancer [4, 5, 82]. Nutrition therapy and exercise prescription have the potential to improve CRF and other prostate cancer disease- and treatment-related side effects [19–21, 25, 83–85]. This clinical trial is the first to investigate the efficacy of nutrition therapy above the healthy eating guidelines in managing prostate CRF. The lack of dietary guidelines for men with prostate cancer is a limitation in the current treatment and management of prostate cancer; thus investigating individual structured nutrition therapy provides novel insight to the efficacy of dietary modification in managing CRF and other side effects from ADT. This project will expand the exercise oncology literature by investigating the efficacy of high intensity interval training for reducing CRF and improving quality of life in men with prostate cancer. Considering both individual nutrition therapy beyond general healthy eating guidelines and high intensity interval training are yet to be investigated in men with prostate cancer, this landmark study will provide novel evidence to support the development of guidelines to optimise the management of CRF and other side effects from ADT. It is hypothesized that nutrition therapy alone, and with high intensity interval training will improve CRF and ADT-related side effects.

Dissemination of the results from this study to oncologists, urologists, prostate cancer nurses, dietitians, nutritionists, exercise physiologists and other exercise specialists will be important to ensure an evidence-based approach to the use of nutrition and exercise in the management of prostate CRF. Currently CRF is managed primarily with medications. Natural therapies such as diet and exercise provide a multi-faceted approach to managing CRF, which may in turn improve other associated side effects seen from ADT (e.g. metabolic and cardiovascular risk). With the rising incidence of prostate cancer and increasing survival rates, the primary outcome from this study will be to provide evidence to enhance clinical practice in nutrition, diet and exercise therapy to improve the lives of men suffering from the disease- and treatment-related side effects of prostate cancer.

